### Ethics, informed consent

The study protocol was approved by the Tel Aviv Sourasky Medical Center Institutional Review Board/ Ethics (Helsinki) Committee, approval number: 0111-13-TLV. Oral and written informed consent from the patient will be obtained prior to inclusion.

### Adverse events

After the procedure, participants are assessed every day until discharge and then at 30 days, 3 months, and 6 months (Table 2). At each of these follow-up visits, the occurrence of adverse events is evaluated by medical interview and review of medical records for every patient.

**Table 2 T2:** Flow chart of the anticipated procedures during the study follow-up

	**Baseline**	**TAVI**^ *** ** ^**procedure**	**Hospitalization**	**Discharge**	**1 month ± 7 days**	**6 months ± 14 days**
Informed consent	**√**					
Full medical history	**√**					
Physical examination	**√**		**√**	**√**	**√**	**√**
Blood tests	**√**	**√**	**√**	**√**	**√**	**√**
Endothelial function	**√**					
Urinary analysis	**√**	**√**	**√**			
Carotid doppler	**√**					
12 lead ECG^†^	**√**			**√**		
Cardiac echo	**√**			**√**	**√**	**√**
Adverse events assessment		**√**	**√**	**√**	**√**	**√**

*****TAVI - transcatheter aortic valve implantation; ^†^ECG – electrocardiogram.

The sign **√** indicates the timing at which the procedures listed above are performed.

### Safety

The RenalGuard system is approved for coronary angiography. Since all patients undergoing TAVI undergo urinary catheterization with a Foley catheter, our major safety issue is related to fluid overload. We will assess this issue by evaluating both in-hospital and 30-day readmission rate for congestive heart failure exacerbation, using patient medical records and medical interviews. In addition, we will evaluate all other safety criteria according to the VARC-2 criteria for TAVI procedures [15].

### Interim analysis

An independent DSMB is chartered to monitor and evaluate patient safety to identify any clinically relevant trends, and to recommend whether the study should continue. The DSMB review will occur after 30 randomized patients have completed the 30-day follow-up and after approximately 25%, 50%, and 75% of the cohort has completed their six-month follow-up. An interim analysis for efficacy is planned after 50% of the cohort is enrolled.

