### Randomization and blinding

At the time of enrollment, signed informed consent will be obtained as per the Tel Aviv Medical Center institutional ethical board standards. After signing the informed consent, patients will be randomized in a 1:1 fashion using closed envelopes. They will be randomized to the active use of RenalGuard system versus using passive use of the RenalGuard system using normal saline 0.9% infusion (sham-controlled group) (Figure 2). The RenalGuard system will be covered before, during and after the procedure with a bag in order to allow effective blinding. All participants will remain blinded throughout the 6-month study period. The interventional cardiologist conducting the TAVI procedure is also blinded to the study treatment arm. The supervising physician, core labs, the biostatisticians performing the analysis, the members of the Clinical Event Committee (CEC), as well as the members of the Data Safety Monitoring Board (DSMB) are blinded to treatment assignment until study completion and after the database has been unlocked.

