### Power analysis

The study is powered to detect a 50% reduction in AKI between the groups. The following assumptions and hypotheses correspond to the primary objective:

A = 40% of participants in the sham-controlled group will develop AKI.

B = 20% of participants in the active group will develop AKI.

Hypotheses:

H0: A = B

H1: A ≠ B

Type I error rate = 5% (2-sided) with power = 80%

Drop out/lost to follow –up, rate = 5%

Under the assumption that AKI is relatively common (40%) after TAVI, and that the RenalGuard system has been shown to reduce the incidence of AKI by up to 70% [3,4], we estimated that if there will be a 50% reduction in AKI in the RenalGuard group, the number of patients needed in each group to attain 80% power with an alpha of 0.05, is 92. We plan on recruiting 110 patients in each group (220 total) in order to assure achieving statistical power.

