### Statistical analysis

Standard statistical analyses will be used to compare the aforementioned endpoints in both study arms. We will compare the incidence of AKI and any clinical differences between the groups. Between-group comparisons of clinical endpoints, biomarkers, and imaging data will be performed using the Mann-Whitney U, independent Student’s t tests, or chi square test according to the distribution of variables. All values will be expressed as medians and interquartile ranges for non-normally distributed continuous variables and as mean and standard error for normally distributed variables.

The statistical analysis of the primary endpoint will performed and presented following the intent-to-treat (ITT) principle. A second set of analysis will be performed using a per-protocol population which will include all enrolled patients who completed the procedure and had a 6-month follow-up. Reported *P* values will be two-sided, and *P* <0.05 will be considered as statistically significant. All analyses will be performed using SPSS statistical software.

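### An efficacy interim at half enrolment sits beside a single unadjusted P<0.05 rule: if that rule is used at both looks, the promised 5% type I error becomes about 8.3%

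*Protocol article*

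**What the plan says.** Three sections of the protocol article bear on this.

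- **Interim analysis.** After describing the safety reviews of the monitoring board, the section adds a separate item: "An interim analysis for efficacy is planned after 50% of the cohort is enrolled". It gives no significance level, boundary or stopping rule for that analysis.
- **Power analysis.** The error rates are set as "Type I error rate = 5% (2-sided) with power = 80" (per cent). The assumed event rates are "A = 40% of participants in the sham-controlled group will develop AKI" and "B = 20% of participants in the active group will develop AKI". The resulting size is stated as "the number of patients needed in each group to attain 80% power with an alpha of 0.05, is 92", with 110 per group to be recruited. The section does not mention the interim look.
- **Statistical analysis.** The only significance rule in the article is that reported P values are two-sided and that P "<0.05 will be considered as statistically significant". It makes no exception for the interim and sets no reduced level for the final test.

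The primary endpoint, acute kidney injury, is read at 48 to 72 hours (Primary endpoint section). Nearly every patient enrolled by the interim will therefore have an outcome.

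**The concern.** A plan that tests the same null hypothesis twice, each time at the full two-sided 5%, has more than a 5% chance of a false positive. Here the article fixes a level, promises that level overall, and also adds an efficacy look. Read literally, the one printed rule applies to the interim P value as well as the final one, and the promise is then not kept.

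At stake is whether a chance result at about 110 patients could count as evidence of benefit. Timing matters too. A boundary fixed before the interim is routine, but one chosen after efficacy data have been seen is open to challenge. The Trial status section reports 41 patients recruited, so at that date the interim was still ahead.

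**Working it through.** **Inputs.** From the Power analysis section: 40% and 20% event rates, two-sided alpha 0.05, power 80%, 5% loss, 92 per group needed and 110 recruited. From the Randomization and blinding section: "patients will be randomized in a 1:1 fashion using closed envelopes". From the Interim analysis section: one efficacy look at 50% enrolment, that is 110 of 220 patients, or about 55 per group. Because the outcome is known within 72 hours, the information fraction t is taken as 0.5.

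**Step 1: is the stated sample size a single-look figure?** The pooled two-proportion formula, with mean rate 0.30 and difference 0.20, gives

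n = [1.960·√(2·0.3·0.7) + 0.842·√(0.4·0.6 + 0.2·0.8)]² / 0.2² = (1.270 + 0.532)² / 0.04 = 81.2, rounded up to 82.

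The continuity correction is n/4·[1 + √(1 + 4/(n·0.2))]². It gives 91 from the unrounded n and 91.7, or 92, from n = 82. The plan's 92 is therefore reproduced as a fixed design with one test at the full 0.05 and no allowance for an interim. Adding 5% loss gives 92/0.95 = 96.8, or 97, so 110 per group leaves a surplus.

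**Step 2: overall type I error with two looks.** Under the null, the interim and final test statistics are approximately bivariate normal with correlation √t = √0.5. The overall error is

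1 − P(|Z₁| ≤ c₁ and |Z₂| ≤ c₂).

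With c₁ = c₂ = 1.96 this is 0.0831. Equivalently, 0.05 + 0.05 minus the 0.0169 chance of crossing at both looks. At t = 0.4 it is 8.6% and at t = 0.6 it is 8.0%.

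Simulated uncorrected chi-square tests agree. With 55 then 110 per group, they give 8.2% to 8.4% for common event rates of 20% to 40%. With 52 then 104 per group (about 5% lost), they give 8.3% to 9.1%. The upper figure reflects discreteness, since the single tests themselves run at 5.7% and 5.2% there.

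**Step 3: dependence on the unstated interim rule.** Two looks, t = 0.5:

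| Interim level for a claim | Final level | Overall type I error |
|---|---|---|
| none (no claim possible) | 0.05 | 5.0% |
| 0.001 (Haybittle-Peto) | 0.05 | 5.02% |
| 0.0052 | 0.05 | 5.2% |
| 0.0052 (O'Brien-Fleming, abs. z > 2.797) | 0.0480 (abs. z > 1.977) | 5.0% |
| 0.0294 (Pocock) | 0.0294 | 5.0% |
| 0.05 | 0.05 | 8.3% |

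**Step 4: cost in power.** For 40% against 20%, the power of the final test alone is as follows.

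| Per group | Final level 0.05 | O'Brien-Fleming final level | Pocock final level |
|---|---|---|---|
| 110 | 90.5% | 90.2% | 86.1% |
| 104 | 88.8% | 88.5% | 84.0% |

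The O'Brien-Fleming loss is about 0.3 points, and every entry stays above the planned 80%.

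**The case against.** The strongest reply is that the article nowhere says the interim will be judged at P<0.05, or that crossing any level permits a claim or stops the trial. The P<0.05 sentence can be read as a general reporting convention. The monitoring board's remit is patient safety and whether to continue. The biostatisticians and the board are to stay blinded to allocation until the study is complete. Interim boundaries often sit in an analysis plan or board charter, and the article mentions that the board is chartered. Under a Haybittle-Peto rule, the printed 5% and the printed final level would both survive almost unchanged.

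Much of this stands, and it rules out three stronger readings.

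- A reader might infer that the trial's type I error simply is 8.3%. That needs two premises the article does not state: an interim level of 0.05, and permission to claim efficacy on it.
- A reader might count the monitoring board's reviews as further efficacy looks. The article describes them as safety reviews and lists one efficacy interim separately. Apart from the first review, after 30 patients, they are triggered by six-month follow-up, so they would not be equally spaced in primary-endpoint information either.
- A reader might say that a final P between 0.048 and 0.05 would be claimed on alpha already spent. That presumes an O'Brien-Fleming boundary, and the article chooses none.

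The reply does not remove the point. The article does not leave the level open: it fixes 0.05 without restriction while adding an efficacy look. If an unseen document holds an O'Brien-Fleming or Pocock boundary, the printed 0.05 is wrong for the final primary test. If it holds a strict interim level, the printed 0.05 is wrong for the interim P value. Blinding to allocation does not prevent a comparison of coded arms.

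**Conclusion.** The point holds in conditional form. The article plans an efficacy interim, promises a 5% two-sided error with a single-look sample size, and prints only an unadjusted P<0.05. Applied at both looks, with either able to support a claim, that rule gives about 8.3%, roughly two-thirds above the stated 5% (8.31/5 = 1.66). If the interim cannot lead to a claim the error is 5.0%, and with an interim level of 0.001 it is 5.02%. Which value applies depends on a rule the article does not state.

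The figures assume one efficacy interim at about half the information and a final test at 0.05. Moving the information fraction between 0.4 and 0.6 changes 8.3% only to between 8.6% and 8.0%.

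**What to change.** Before the 110-patient interim, amend the Interim analysis and Statistical analysis sections in one of two ways.

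1. **State one group-sequential rule for the primary endpoint.** For example, O'Brien-Fleming with interim P<0.0052 and final P<0.048, or Haybittle-Peto with interim P<0.001 and final about 0.05.
2. **State that the interim cannot lead to an efficacy claim or to stopping for efficacy.** The final test then keeps 0.05.

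In either case, limit the general P<0.05 sentence to analyses outside the chosen rule. If a boundary already exists in an analysis plan or board charter, quote it in the protocol and align the sentence with it.

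The cost is one or two sentences. With the rules named above, the final threshold falls to about 0.048 at the lowest, power drops by about 0.3 points, and no extra patients are needed.

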### Power analysis

The study is powered to detect a 50% reduction in AKI between the groups. The following assumptions and hypotheses correspond to the primary objective:

A = 40% of participants in the sham-controlled group will develop AKI.

B = 20% of participants in the active group will develop AKI.

Hypotheses:

H0: A = B

H1: A ≠ B

Type I error rate = 5% (2-sided) with power = 80%

Drop out/lost to follow –up, rate = 5%

Under the assumption that AKI is relatively common (40%) after TAVI, and that the RenalGuard system has been shown to reduce the incidence of AKI by up to 70% [3,4], we estimated that if there will be a 50% reduction in AKI in the RenalGuard group, the number of patients needed in each group to attain 80% power with an alpha of 0.05, is 92. We plan on recruiting 110 patients in each group (220 total) in order to assure achieving statistical power.

### Statistical analysis

Standard statistical analyses will be used to compare the aforementioned endpoints in both study arms. We will compare the incidence of AKI and any clinical differences between the groups. Between-group comparisons of clinical endpoints, biomarkers, and imaging data will be performed using the Mann-Whitney U, independent Student’s t tests, or chi square test according to the distribution of variables. All values will be expressed as medians and interquartile ranges for non-normally distributed continuous variables and as mean and standard error for normally distributed variables.

The statistical analysis of the primary endpoint will performed and presented following the intent-to-treat (ITT) principle. A second set of analysis will be performed using a per-protocol population which will include all enrolled patients who completed the procedure and had a 6-month follow-up. Reported *P* values will be two-sided, and *P* <0.05 will be considered as statistically significant. All analyses will be performed using SPSS statistical software.

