**Figure 3 F3:**
[figure not shown]
Treatment algorithms of the sham-controlled/passive RenalGuard group (group A) and the active RenalGuard group (group B).

Before the procedure: A standard 18 to 22 gauge catheter will be inserted into a peripheral vein of the arm and a standard Foley catheter will be placed in the bladder for urine collection (as performed routinely for all TAVI procedures). The intravenous (IV) line and the urinary catheter will be connected to the RenalGuard System. The RenalGuard System will be set to 0% match; that is, the urine rate and volume will be measured, but it will not deliver matched IV normal saline. The system will be computed to deliver continues IV normal saline at a rate of 100 cc/h (100 cc/h is the routine average fluid infusion rate in TAVI procedure) during the procedure and up to 6 h after the procedure. Neither a routine IV bolus of saline nor a routine IV furosemide will be given before the procedure.

During the procedure: The urine and infusion volumes will be measured by the RenalGuard system throughout the catheterization procedure and for 6 h after the last contrast dose. Additional IV fluids can be added as needed according to the clinical decision of the anesthesiologist or the attending physician.

We will analyze the quantity and quality of urine during the duration of the procedure.

**Group 2** - Active Group (Figure 3B). Treatment as group 1 and in addition, the RenalGuard system will be activated (active mode).

Before the procedure: A standard 18 to 22 gauge catheter will be inserted into a peripheral vein of the arm and a standard Foley catheter will be placed in the bladder for urine collection (as performed routinely for all TAVI procedures). The IV line and the urinary catheter will be connected to the RenalGuard System. The RenalGuard System will be set to 100% match; that is, the urine rate and volume will be measured and the system will deliver volume of IV normal saline that is matched to the volume of urine produced by the patient. An initial IV bolus (250 ml) of normal saline over 30 min will be administered approximately 90 min before the procedure; in patients with heart failure, the volume of the bolus can be reduced to 150 ml. Furosemide will then be administered as a single intravenous bolus of 0.25 to 0.5 mg/kg at the physician’s discretion. When a urine output rate >300 ml/h will be achieved, the patients will be sent to the catheterization laboratory.

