### Blood and urinary samples

Blood samples will be taken at baseline (on admission); before the procedure; and at 6, 12, 24, 48, and 72 h post-procedure. An 18-gauge cannula will be placed in an antecubital vein for blood sampling. Blood sample analyses will be performed using reagents, calibrators and control materials from Bayer Diagnostics (Berkshire, England) on the ADVIA 1650. At baseline each Patient will provide 40 cc of blood for the following blood tests: full chemistry including lipid levels, thyroid function, BNP, NT-BNP, HbA1c, uric acid, and glucose levels; complete blood count; inflammatory biomarker (hs-CRP, fibrinogen, IL-6, IL-1, MMP, Lp-PLA2, procalcitonin, IL-10, IL-35, TNFa, AchE, and cholinergic status); renal function markers including creatinine, NGAL (neutrophil gelatinase-associated lipocalin), FGF23, and Cystatin-C; and endothelial function markers including I-CAM, V-CAM, superoxide dismutase ADMA, and oxidized LDL. Serum and plasma samples will be frozen for future tests.

Urine samples will be taken at baseline (before the procedure), and after 24 h.

Samples will be taken for basic urinalysis, creatinine, albumin, microalbumin, and electrolytes.

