### Primary endpoint

The primary endpoint is reduction of acute kidney injury (stage 1 or above) at 48 to 72 h. Serum creatinine level will be measured prior to TAVI and at 48 to 72 h post-procedure. AKI will be defined as stage 1, 2 or 3 according to VARC-2 AKI classification [15] (Table 1).

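### The urine sampling times contradict the promised procedural urine analysis, and the between-group tests of biomarkers and imaging are not limited to measures with post-procedure values (minor)

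*Protocol article*

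**What the plan says.** **Urine.** The description of each arm under Study protocol contains the sentence "We will analyze the quantity and quality of urine during the duration of the procedure". Table 2 (under Adverse events) ticks urinary analysis at baseline, at the TAVI procedure and during hospitalization. The section Blood and urinary samples gives different times: "Urine samples will be taken at baseline (before the procedure), and after 24 h". It lists urine creatinine, albumin, microalbumin and electrolytes among the assays.

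**Blood markers.** Draws are scheduled on admission, then "before the procedure; and at 6, 12, 24, 48, and 72 h post-procedure". The inflammatory, renal and endothelial panel is introduced by "At baseline each Patient will provide 40 cc of blood for the following blood tests". No analyte list is given for the later draws. The section adds that "Serum and plasma samples will be frozen for future tests", without saying from which time points. The Primary endpoint section supplies one further analyte: "Serum creatinine level will be measured prior to TAVI and at 48 to 72 h post-procedure". Table 2 ticks blood tests in every column without naming assays.

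**Vascular measures and echo.** Table 2 ticks endothelial function and carotid Doppler at baseline only. It ticks cardiac echo at baseline, discharge, 1 month and 6 months.

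**Analysis.** The Statistical analysis section says "Between-group comparisons of clinical endpoints, biomarkers, and imaging data will be performed", using the Mann-Whitney, t or chi-square test. It does not mention adjustment for baseline and does not name urine. Secondary endpoints gives EndoPat, carotid Doppler and the biomarkers a predictive purpose.

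**The concern.** There are two separate problems.

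First, an analysis is promised for a period in which the sampling section collects no specimen. A team working from that section would have urine volume from the device but nothing to assay for quality. Urine that is not kept cannot be recovered later.

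Second, the analysis sentence covers biomarkers and imaging as whole classes, although some of these measures are scheduled only before the arms diverge. A P value from such a comparison could be reported beside treatment comparisons and read as one, although it says nothing about the device.

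A further question follows if procedural urine is obtained. The active arm is driven to a high urine flow and the sham arm is not, so raw concentrations differ between arms partly through volume.

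**Working it through.** The plan gives no figure on this point to reproduce. Its 92 per group is derived from AKI proportions of 40% and 20% and uses none of the measures discussed here (recalculation gives 91 with a continuity correction, 82 without). The check is therefore a comparison of sections.

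**1. Urine during the procedure**

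| Place | Procedural specimen? |
|---|---|
| Study protocol, both arm descriptions | Yes: quality is to be analysed over the procedure |
| Table 2, urinary analysis | Yes: ticked at TAVI |
| Blood and urinary samples | No: baseline and 24 h only |

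The 24 h sample cannot stand in for procedural urine. Matched hydration stops 6 h after the last contrast dose. If the 24 h is counted from about that dose (the article does not state its origin), the sample is taken 24 − 6 = 18 h after matching ends.

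**2. What a baseline-only comparison can show**

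Let X be a value measured before treatment. Under randomisation E(X | active) = E(X | sham), whatever the treatment does. A 5% test of X then rejects in about 5% of trials whether the effect is zero or large, so it carries no information on efficacy.

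| Measure | Post-procedure value stated? | Can a between-arm test address treatment? |
|---|---|---|
| Carotid Doppler, EndoPat | No | No |
| Marker panel other than creatinine | Not stated; later draws and frozen samples exist | Only if assayed later |
| Serum creatinine | Yes, 48 to 72 h | Yes |
| Cardiac echo | Yes, discharge, 1 and 6 months | Yes |

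Where both a baseline and a later value exist, the listed two-sample tests ignore the baseline. Adjusting for it by analysis of covariance multiplies the residual variance by about 1 − ρ², where ρ is the correlation between baseline and follow-up. The article gives no ρ, so no gain is quoted.

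**3. Comparing procedural urine between arms**

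Write concentration C = E/V, with E the amount excreted and V the urine volume. Then

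C(active)/C(sham) = [E(active)/E(sham)] × [V(sham)/V(active)].

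The second factor differs from 1 by design, because the active arm is managed to a urine output above 300 ml/h and the sham arm has no such target. Two measures remove V:

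- Amount excreted: E = C × V. The device records V in both arms.
- Ratio to urine creatinine: C/C(creatinine) = E/E(creatinine). V cancels, provided creatinine excretion is comparable between arms.

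**The case against.** **Later marker assays are unspecified, not excluded.** Five post-procedure draws are scheduled, samples are frozen, and an article commonly leaves the assay list per time point to the full protocol. This stands. A reader might infer that the trial will have no post-procedure biomarker values, or that none of these comparisons can show a treatment effect. The document supports neither. Creatinine is measured afterwards, echo is repeated, and the 24 h urine sample is itself post-treatment.

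**The imaging sentence has a valid object, and the vascular measures fit their purpose.** Echo gives the sentence something proper to test, and prediction of AKI needs only baseline values. Both statements are correct. What remains is that the sentence does not confine itself to echo.

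**Urine is not among the named comparisons.** True: the arm descriptions say only that urine will be analysed. The contradiction on sampling times stands regardless. The advice on concentration applies only if arms are compared, and the quantities it needs are already collected.

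**Tempting numbers.** Counting 21 panel markers gives 21 × 0.05 = 1.05 expected chance differences and 1 − 0.95^21 = 66% for at least one. That count includes creatinine, which has a later value. With 20 the result is 1 − 0.95^20 = 64%, still assuming independence, which is implausible for related inflammatory markers. A chance baseline difference also does not itself bias an efficacy result.

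Likewise, an assumed sham flow of 60 to 100 ml/h gives a dilution of 300/100 = 3 to 300/60 = 5 times. The sham flow is not in the article, and the figure needs equal excretion in both arms. The Discussion says furosemide blocks sodium reabsorption, so for electrolytes that cannot be presumed. Neither number measures the size of this point.

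**More assays.** Requests for additional injury markers or serum electrolytes at given hours would be preferences. The document contains no error there.

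**Conclusion.** The point holds in limited form and is minor.

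- The urine passages contradict one another. If the sampling section is followed, the promised analysis of procedural urine quality cannot be done. This rests on stated text alone.
- The between-group sentence is too broad. For carotid Doppler, and for EndoPat if it is counted with these data, an arm comparison shows only randomisation balance. The same holds for any panel marker that is in fact assayed at baseline alone, which the article leaves open.
- If procedural urine is compared between arms, raw concentration is the wrong scale because urine flow differs by design. The direction and size of any distortion cannot be derived from the article.

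Only secondary or exploratory analyses are touched. The primary AKI endpoint and the planned 110 per group are unaffected.

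**What to change.** 1. **Reconcile the urine times** across the arm descriptions, Blood and urinary samples and Table 2. One way is to add to the sampling section a single aliquot from the mixed catheter collection at the end of the procedure, with the same defined collection interval in both arms. If no procedural specimen is intended, remove the promise and the tick.
2. **Fix the urine scale.** State that any between-arm comparison of procedural urine uses amount excreted (concentration × device-measured volume over the same interval) or the ratio to urine creatinine.
3. **Narrow the Statistical analysis sentence.** Limit between-group tests to measures with post-procedure values: echo, creatinine, and any markers assayed at the scheduled later draws or from frozen samples. Adjust each for its baseline value. Use baseline-only measures solely as predictors, as Secondary endpoints already intends.

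**Cost.** One urine aliquot assay per patient and a little more analysis work, with no new visit, blood draw or catheter. The article reports 41 of 220 patients recruited, so at that date 220 − 41 = 179 could still contribute a procedural sample. Patients already treated without one would be missing from that analysis.
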